#### Main outcome

The primary outcome is decisional conflict, measured by the Decisional Conflict Scale (DCS) [46]. Decisional conflict is defined as a state of uncertainty about the course of action to take [61]. The DCS measures how well-informed patients feel about their decision, the level of uncertainty about the best choice, and the perceived effectiveness of decision making. It has a total scale and five subscales (uncertainty, feeling informed, feeling clear about values, feeling supported and effective decision-making). Items belonging to the subscale effective decision-making will not be assessed at baseline, since these items were considered inappropriate to assess before patients had a consultation with a plastic surgeon. The DCS is reliable and valid [46–48], and is the most commonly used instrument to evaluate effectiveness of pDAs [62].

#### Secondary outcomes

##### Decision-making process and decision quality

The decision-making process is further measured in terms of I) satisfaction with information [49], II) satisfaction with the plastic surgeon [49], III) preparedness for decision making [50, 51], IV) patients’ perceived levels of shared decision making during consultation with their plastic surgeon [52, 53], and V) patients’ perceived level of involvement in decision making [54]. Decision quality is measured by I) knowledge of breast reconstruction [36, 55] and II) decision regret [56, 57].

##### Patient-reported health outcomes

Patients’ actual choice regarding breast reconstruction will be measured by patient-report at postsurgical follow-up (T2, T3), and will be verified against patients’ EMR. Patient satisfaction with the breast [49], body image [58], sexual functioning [58], and breast symptoms [58] will be obtained at postsurgical follow-up. Anxiety will be measured at all four time points [59].

### Moderating measures

At baseline, we will measure patients’ preferred level of involvement in decision making regarding breast reconstruction (Control Preferences Scale [54]), preference for breast reconstruction (1 item, 5 point Likert-type Scale, with 1 = “I have a strong preference for undergoing breast reconstruction”, and 5 =“I have a strong preference for not undergoing breast reconstruction”) and information coping style (Threatening Medical Situations Inventory [63]). At all assessments, patients will be asked to report on the information sources they used regarding breast reconstruction.

### Process measures

Among women in the intervention group, the actual usage of the pDA (i.e. whether and when they logged in, whether the summary sheet was discussed with a plastic surgeon) will be obtained via self-report at T1. Usage data will be supplemented with log data collected in the pDA (e.g., number of logins, number of completed modules). Additionally, at T1, all participants will report on how satisfied they are with the received information (i.e., pDA or information leaflet) and how useful it was for them in making a decision about breast reconstruction.

### Cost-effectiveness

For the cost-effectiveness analysis we will determine incremental costs, incremental effects (in terms of quality adjusted life years (QALYs), reduction in decisional conflict, reduction of regret), and the incremental cost-effectiveness ratio.

#### Utilities

QALYs are calculated by multiplying the life years with the utilities. An utility is a score that is derived from the generic five-level EuroQol five-dimensional questionnaire (EQ-5D-5 L) [60]. This preference based instrument consists of five dimensions: mobility, self-care, usual activities, pain/discomfort and anxiety/depression [60, 64].

#### Costs

Unit costs will be estimated based on the trial data and published sources in the Netherlands [65]. Fixed costs of the development of the pDA will be based on the R&D of the pDA, including expected maintenance costs. For the control group, costs of a leaflet will be taken into account. Direct medical costs will include (1) treatment costs: type and number of (reconstructive) breast surgeries during study participation (data collected from the EMR), number of nights hospitalized (EMR)/inpatient days in hospital (for any reason) (EMR), and (2) resource use: participants are asked for professional care resources they used related to their breast (reconstructive) surgery. This consists of the number of consultations (live or by phone) with plastic surgeons and other medical and paramedical professionals pre- and post-operatively. For medical consumption, patients are asked to report on the received amount of home care (selection of items of the iMTA Medical Consumption Questionnaire on T2 3 months after surgery and T3 12 months after surgery; see https://www.imta.nl/). Production losses are measured by means of work status at T2 and T3, controlled for work status at baseline, and the number of hours in sick leave.

### Randomization

Simple randomization stratified by site and patients’ surgical treatment options (e.g., whether the patient is eligible for both mastectomy and BCS or for mastectomy only) will be used to assign participants to the intervention group or the control group. Randomization ratio is 1:1. Randomization will be performed with ALEA software. This study is non-blinded, since blinding was not considered feasible due to the nature of the trial.

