### Study setting

The study will be conducted in eight hospitals (two academic centres, five general hospitals and one cancer-specialized hospital) throughout the Netherlands.

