### Statistical analyses

Data will be pseudonymized prior to data analysis and will not be traceable to any individuals. Depending on the level of measurement, analysis of variance or appropriate non-parametric statistics will be used to evaluate the comparability of baseline sociodemographic and clinical characteristics between the intervention and the control group. If differences in background characteristics are found, these will be taken into account in the subsequent analyses. Scores on the questionnaires will be calculated according to published scoring algorithms.

We will look at group differences in decisional conflict for the entire study duration (T0 to T3) using a mixed effect growth model with random intercept and slope and site as a cluster variable. This approach takes into account the within and between person variability, and deals adequately with missing data [66]. A comparable mixed effect model approach will also be used to determine the effects of the pDA on other patient reported outcomes. Differences in mean change scores over time between the intervention and control group will be accompanied by effect sizes (ES). An ES of 0.2 is considered small, 0.5 moderate and 0.8 large [67].

Analyses will be done on an intention-to-treat basis. As a secondary analysis, per-protocol analyses will be carried out on data from patients who meet the criteria for minimal compliance (to be determined). Appropriate statistical measures will be taken to adjust for multiple comparisons.

To evaluate between-group differences over time in categorical variables such as the actual choice in breast reconstruction, generalized estimating equations for longitudinal data will be used. This approach accounts for correlated within subject responses, allows for not normally distributed variables and deals adequately with missing data [68, 69].

We will explore which variables are predictive for the efficacy of the pDA on the primary outcome (decisional conflict) within the intervention group. A mixed effect model for longitudinal data will be used with decisional conflict as dependent variable and the following independent (baseline) variables: knowledge of breast reconstruction, patients’ preferred level of involvement in decision making, information coping style, and sociodemographic variables. The *p*-values for each model will be adjusted for multiple comparisons.

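### The allocation scheme is described inconsistently ('simple' yet 'stratified'), and the primary model carries site but not the second stratification factor, at a modest cost in precision

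*Protocol article*

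**What the plan says.** In the protocol article, the Randomization section gives the method as "Simple randomization stratified by site and patients’ surgical treatment options". The second factor is introduced only as an example: "whether the patient is eligible for both mastectomy and BCS or for mastectomy only". The section adds "Randomization ratio is 1:1" and "Randomization will be performed with ALEA software". It names no block, minimisation or other restriction.

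Under Study setting, "The study will be conducted in eight hospitals".

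The Statistical analyses section says decisional conflict will be analysed "using a mixed effect growth model with random intercept and slope and site as a cluster variable". Surgical treatment option is not named in that model, and other patient-reported outcomes are to be analysed by a comparable approach. The one general provision on covariates is "If differences in background characteristics are found, these will be taken into account in the subsequent analyses".

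The section on sociodemographic and clinical data lists eligibility for breast-conserving surgery (BCS) among the items in the baseline questionnaire.

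**The concern.** There are two linked problems.

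**The description.** Simple randomisation is an independent 1:1 draw for each woman. Labelling the draws by stratum does not change their joint distribution. Stratification has an effect only if allocation is restricted within strata, for example by permuted blocks, or is steered by minimisation on the factors. As written, a reader cannot tell which design was run, and the levels of the second factor are not fixed.

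**The analysis.** One of the two stratification factors is carried into the model and the other is not. The only way in for the second is a rule driven by observed baseline differences. If stratification works, little difference will be seen and the factor will tend to stay out. Yet under restricted allocation that is when omitting a prognostic factor makes the standard error too large.

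At stake are precision, an accurate account of the design, and a model settled in advance instead of by baseline testing.

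**Working it through.** **1. The plan's own figure.** With d = 0.4, two-sided alpha 0.05 and power 0.80, n per arm = 2 × (1.960 + 0.842)² / 0.4² = 98.1, rounded up to 99, so 198 in total. Allowing for 20% attrition, 198 / 0.8 = 247.5, or 248, against the stated 250. The figures reproduce, and this point does not alter them.

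**2. The literal scheme.** Eight hospitals × 2 assumed levels = 16 strata, and 250 / 16 = 15.6 women on average. Under independent 1:1 draws, the exact binomial chance of a 60:40 or worse split is:
- 45% in a stratum of 16
- 28% in a site of 31 (250 / 8)
- 0.2% in the whole trial of 250

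These are the figures for unstratified allocation, so the stratification does nothing.

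**3. Balance on the factor itself.** For the pooled comparison, what matters is the difference between arms in the share of BCS-eligible women. In simulation (N = 200, 16 strata, 4,000 runs per setting), simple allocation gave a gap of 10 points or more in about 7–8% of trials at an assumed prevalence of 20%, and in about 16–17% at 50%. Blocks of 4 within strata gave none.

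**4. Leaving the factor out.** The same simulation used a linear model at a single time point, total SD 1, treatment effect 0.4 SD and no site effect. The article gives neither the prevalence nor the factor effect, so both are assumed over a range.

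| Prevalence | Factor effect (SD) | Blocked: type I error, factor omitted | Blocked: power, omitted → included | Simple: type I error, factor omitted | Simple: power, omitted → included |
|---|---|---|---|---|---|
| 20% | 0.2 | 0.047 | 0.808 → 0.810 | 0.052 | 0.807 → 0.804 |
| 20% | 0.5 | 0.049 | 0.802 → 0.812 | 0.048 | 0.803 → 0.812 |
| 20% | 0.8 | 0.041 | 0.809 → 0.842 | 0.044 | 0.793 → 0.835 |
| 50% | 0.2 | 0.052 | 0.803 → 0.806 | 0.054 | 0.803 → 0.804 |
| 50% | 0.5 | 0.041 | 0.817 → 0.838 | 0.045 | 0.803 → 0.825 |
| 50% | 0.8 | 0.036 | 0.831 → 0.878 | 0.054 | 0.803 → 0.870 |

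The Monte Carlo standard error at 0.05 is √(0.05 × 0.95 / 4000) = 0.003.

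**5. Check by formula on the last row.** The factor explains 0.8² × 0.5 × 0.5 = 0.16 of the variance.
- With perfect balance, the unadjusted standard error is too large by 1/√0.84 = 1.09. The effective critical value is 1.96 × 1.09 = 2.14, which gives a type I error of about 0.032. Incomplete blocks bring this closer to the simulated 0.036.
- With the factor included, power is Φ(0.4 × √(200/4) / √0.84 − 1.96) = Φ(1.13) = 0.87.
- With the factor omitted, power is Φ(3.09 − 2.14) = 0.83 under blocking and Φ(2.83 − 1.96) = 0.81 under simple allocation.

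These agree with the simulation.

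**The case against.** The strongest reply is that this is largely the shorthand of a journal article. 'Simple' may be loose wording for blocks or minimisation run in the named software, and block details and the full covariate list commonly sit in a fuller document that is not shown. This stands in part: absent block sizes are no fault. But the article does name a scheme, and names it in terms that cannot both apply. It also fixes how covariates enter, by observed difference, and that suits a stratification factor badly.

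Three stronger readings are tempting, and the document does not support them.
- *A promised balance is not delivered.* The Randomization section names a method and two factors. It makes no explicit claim about balance.
- *Chance imbalance would go uncorrected.* BCS eligibility is among the baseline data, and differences found at baseline are to be taken into account. The rule is weaker than a pre-specified term, but it is there.
- *Lopsided strata bias the result.* Uneven splits within single strata do not bias the pooled effect. An overall split of 110:140, the edge of the 95% range, still keeps 4 × 0.44 × 0.56 = 98.6% of the information. At 198 women and d = 0.4 that costs about 0.6 points of power.

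It is also fair that decisional conflict is measured at T0 and modelled from T0 to T3 with a random intercept. A stable difference by BCS eligibility, already present at T0, would be partly absorbed, so the gains above may be overstated for the actual model. And the article gives no figure showing that BCS eligibility affects decisional conflict.

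Finally, moving to blocks has a price. The trial is open, blocks in small strata are partly predictable, and retrospective registration suggests that recruitment may already have begun. This argues against requiring a new scheme. It does not argue against naming the one in use.

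**Conclusion.** The point holds as a defect of description and efficiency. The stated scheme is internally inconsistent, the second factor is defined only by example, and the primary model is not pre-specified to include that factor.

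Validity is not threatened. With the factor omitted, simulated type I error stayed at about 0.044 to 0.054 under simple allocation and 0.036 to 0.052 under blocking, at worst slightly conservative. The power forgone runs from nothing, at a factor effect of 0.2 SD, to about 5 points under blocking and about 7 under simple allocation, at 0.8 SD and 50% prevalence.

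These sizes rest on assumed prevalence, factor effect, two factor levels and roughly equal strata, and on a single-time-point model instead of the planned growth model. The 198 and 250 stand.

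**What to change.** 1. **Model.** Pre-specify the surgical-option stratum (eligible for both mastectomy and BCS, or for mastectomy only) as a fixed effect alongside site in the primary and secondary models, regardless of observed imbalance. Because the primary model spans T0 to T3, also decide in advance whether the factor has a term with time. A main effect alone does little for a difference that appears after T0.
2. **Description.** In the Randomization section, name the scheme that the software actually applies, such as blocks within strata or minimisation on both factors. If allocation is unrestricted, drop the word 'stratified' and still adjust for both factors.
3. **Definition.** State the levels of the second factor outright, not by example.

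The cost is a corrected sentence and one or two model terms. BCS eligibility is already collected at baseline, so no new data are needed. The sample size does not change, and the allocation scheme of an ongoing trial need not be altered.

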### Statistical analyses

Data will be pseudonymized prior to data analysis and will not be traceable to any individuals. Depending on the level of measurement, analysis of variance or appropriate non-parametric statistics will be used to evaluate the comparability of baseline sociodemographic and clinical characteristics between the intervention and the control group. If differences in background characteristics are found, these will be taken into account in the subsequent analyses. Scores on the questionnaires will be calculated according to published scoring algorithms.

We will look at group differences in decisional conflict for the entire study duration (T0 to T3) using a mixed effect growth model with random intercept and slope and site as a cluster variable. This approach takes into account the within and between person variability, and deals adequately with missing data [66]. A comparable mixed effect model approach will also be used to determine the effects of the pDA on other patient reported outcomes. Differences in mean change scores over time between the intervention and control group will be accompanied by effect sizes (ES). An ES of 0.2 is considered small, 0.5 moderate and 0.8 large [67].

Analyses will be done on an intention-to-treat basis. As a secondary analysis, per-protocol analyses will be carried out on data from patients who meet the criteria for minimal compliance (to be determined). Appropriate statistical measures will be taken to adjust for multiple comparisons.

To evaluate between-group differences over time in categorical variables such as the actual choice in breast reconstruction, generalized estimating equations for longitudinal data will be used. This approach accounts for correlated within subject responses, allows for not normally distributed variables and deals adequately with missing data [68, 69].

We will explore which variables are predictive for the efficacy of the pDA on the primary outcome (decisional conflict) within the intervention group. A mixed effect model for longitudinal data will be used with decisional conflict as dependent variable and the following independent (baseline) variables: knowledge of breast reconstruction, patients’ preferred level of involvement in decision making, information coping style, and sociodemographic variables. The *p*-values for each model will be adjusted for multiple comparisons.

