## Study measures

### Sociodemographic and clinical data

The patient’s age, country of birth, primary language, marital status, parity, education level, work status, internet experience, hereditary breast cancer risk, history of malignancy, surgery and/or radiotherapy of the breast, neo-adjuvant treatment, surgical risk factors (i.e. weight and height, smoking status, comorbidities), eligibility for BCS and/or nipple-sparing surgery, and indication for adjuvant radiotherapy will be obtained via the baseline questionnaire. Via postsurgical follow-up questionnaires (T2 and T3), we will obtain data on surgical treatment (including type and timing of breast reconstruction, if applicable), complications and adjuvant treatment. Surgical treatment and complications will be verified against data in the electronic medical record (EMR). Date of diagnosis, tumor characteristics, second malignancies and patient’s cup size will be collected from the EMR.

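### The adjustment set for the primary comparison is chosen by comparing randomised arms at baseline instead of being fixed in advance

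*Protocol article*

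**What the plan says.** Statistical analyses opens with a between-arm comparison at baseline: "analysis of variance or appropriate non-parametric statistics will be used to evaluate the comparability of baseline sociodemographic and clinical characteristics". The rule that follows is "If differences in background characteristics are found, these will be taken into account in the subsequent analyses". The next paragraph gives the primary analysis, a comparison of DCS from T0 to T3 "using a mixed effect growth model with random intercept and slope and site as a cluster variable". The rule therefore reaches the primary model, and no other section limits or replaces it.

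Site is the only adjustment factor named for the between-arm models. Randomization describes "Simple randomization stratified by site and patients’ surgical treatment options", so surgical treatment options is a second design factor, and it does not appear in the model. The covariates listed at the end of Statistical analyses belong to the exploratory predictor model within the intervention group, not to the comparison of arms.

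The pool open to the rule is long. Sociodemographic and clinical data runs from age through items such as "internet experience, hereditary breast cancer risk, history of malignancy, surgery and/or radiotherapy of the breast" to surgical risk factors and treatment eligibility.

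**The concern.** Under correct 1:1 randomisation the null hypothesis of every baseline comparison is true, so a test of it cannot tell the analyst which variables to adjust for. What makes adjustment worthwhile is the variable's association with the outcome. A strong predictor of DCS that happens to be balanced stays out under this rule, and an irrelevant variable that differs by luck comes in.

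Two things are at stake. The primary model is not fixed before the data are seen, and with no threshold given, what counts as a difference is left to the analyst. Precision available from prognostic baseline variables is also given up. An SAP could add detail, but it would have to overturn a rule that the protocol states.

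**Working it through.** **1. The plan's own figure.** Power calculation gives power 0.80, alpha 0.05 and d = 0.4. For a two-sided test, n per group = 2(1.960 + 0.842)² / 0.4² = 98.1, or 99 after rounding up, and 198 in total. With 20% attrition, 198 / 0.80 = 247.5, against 250 stated. The figures reproduce. (One-sided alpha would give 78 per group, so the stated size implies a two-sided test.)

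**2. How many variables are open to the rule.** The baseline questionnaire list in Sociodemographic and clinical data gives 17 characteristics if breast and malignancy history counts as one item and weight with height as one. It gives 15 if the surgical risk factors are merged into one item, and 20 if the history is split into three and weight and height are separated.

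**3. Chance of finding at least one difference.** Assumptions: a 5% level (none is stated) and independent variables. P = 1 − 0.95^k.

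- k = 15: 1 − 0.95^15 = 0.537
- k = 17: 1 − 0.95^17 = 0.582
- k = 20: 1 − 0.95^20 = 0.642

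The expected number of spurious differences is 0.05k, which is 0.75 to 1.0. At a 10% level the chance is 79% (k = 15) to 88% (k = 20).

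**4. What the rule does to the analysis.** A simulation used 99 per arm, 17 independent baseline variables of which one has correlation ρ with the outcome, a single-endpoint linear model, and 8,000 trials per setting. The values of ρ are assumptions, since the document gives none.

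| ρ | Power, unadjusted | Power, test-selected covariates | Power, prognostic covariate fixed in advance | Type I error, test-selected |
|---|---|---|---|---|
| 0.3 | 80% | 80% | 83% | 4.7% |
| 0.5 | 81% | 81% | 90% | 4.9% |
| 0.7 | 79% | 81% | 98% | 3.5% |

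About 58% of trials selected at least one covariate. The prognostic one was selected in only about 5%. Each set of 8,000 trials produced roughly 470 to 510 different adjustment sets. The simulation error on a 5% rate is √(0.05 × 0.95 / 8000) = 0.24 percentage points, so type I error under the rule is nominal at ρ = 0.3 and 0.5 and conservative at 0.7.

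The fixed-covariate column agrees with the usual approximation, power = Φ(0.4/√(1 − ρ²) × √(99/2) − 1.96), which gives 84%, 90% and 98%.

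**5. The omitted stratum.** If the stratified allocation balances surgical treatment options as intended, a rule triggered by imbalance will rarely pick it up. If allocation within strata enforces no balance, a 5% test would still select it only about one time in twenty. Either way, a design factor would usually be missing from the model.

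**The case against.** The case on the other side has real force on size and on the remedy.

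- **Power.** A reader might infer that the rule costs the trial the gap between 80% and 90%. The documents do not support that. The calculation compares single-endpoint models at an assumed correlation of 0.5, whereas the planned model runs from T0 to T3 and already holds baseline DCS as a response. The rule concerns sociodemographic and clinical characteristics, so deleting it would not by itself deliver a gain from baseline DCS.
- **Validity.** A reader might also infer that ignoring the selection step inflates the false-positive rate. The simulated type I error is 3.5% to 4.9%, so it does not.
- **Blinding.** The article states "This study is non-blinded, since blinding was not considered feasible due to the nature of the trial", which might suggest that covariates could be picked to suit the result. The written rule selects on baseline data, not on outcomes.
- **The 54% to 64%.** The word significant does not appear, no level is given, and some items are plausibly related, such as country of birth and primary language. Still, naming ANOVA and non-parametric methods makes testing the natural reading, and the absence of a threshold leaves the rule more open, not less.
- **Site.** One of the two design factors is already in the model.
- **Prognostic variables.** The documents identify no established predictor of DCS, so any choice is a judgement to be made in advance.

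What survives is that the protocol fixes a data-dependent covariate rule for its primary comparison and leaves one stratification factor unnamed.

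**Conclusion.** The point holds as one of pre-specification and efficiency, not of invalid inference. Under the assumption of independent 5% tests, at least one chance difference would enter the primary model in 54% to 64% of trials for 15 to 20 characteristics. A truly prognostic variable would enter only about 5% of the time. The estimate would remain a legitimate comparison of randomised arms with nominal or conservative error, but from a model whose covariates were unknown when the plan was written.

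The power figures of about 83%, 90% and 98% at correlations of 0.3, 0.5 and 0.7 are illustrative only. They rest on assumed correlations and a single endpoint, and do not transfer directly to the growth model. The sample size of 198, or 250 recruited, is unaffected.

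**What to change.** - Delete the baseline tests and the conditional-adjustment sentence, and present the baseline table descriptively.
- Name a short covariate set for all between-arm models, used whatever the observed balance: site (already there), the surgical-treatment-options stratum, and one or two baseline variables judged in advance to predict DCS. Preference for reconstruction, listed under Moderating measures, is a candidate.
- Use the T0 score once only: either as a response in the T0 to T3 model with a common baseline mean across arms, or as a covariate in a model of T1 to T3. It should not be both. Main outcome says the effective decision-making items are not asked at baseline, so the T0 DCS is not the same composite as the later totals. The plan should say how it is scored and used.
- Report any adjustment for observed imbalance as a labelled sensitivity analysis.

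Cost: all variables are already collected, and no extra patients are needed. The covariate changes are a matter of wording in the protocol and the SAP. The T0 choice goes slightly further, because it settles the form of the primary model, and it should be made before outcome data are analysed.

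### Reconstruction choice: prespecify adjustment for the baseline preference for reconstruction instead of relying on a rule triggered by observed imbalance

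*Protocol article*

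**What the plan says.** All references are to the protocol article.

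- **Statistical analyses, choice model.** "To evaluate between-group differences over time in categorical variables such as the actual choice in breast reconstruction, generalized estimating equations for longitudinal data will be" the method. The stated merits are: "This approach accounts for correlated within subject responses, allows for not normally distributed variables and deals adequately with missing data". No covariate, stratum or site term is named for it.
- **Statistical analyses, decisional conflict.** Here the model is a "mixed effect growth model with random intercept and slope and site as a cluster variable".
- **Statistical analyses, adjustment rule.** The arms are compared on baseline sociodemographic and clinical variables, and any background variable found to differ is carried into the later analyses. No other adjustment rule for between-arm comparisons is given.
- **Moderating measures.** At T0 each woman rates her "preference for breast reconstruction (1 item, 5 point Likert-type Scale", running from a strong preference for reconstruction to a strong preference against it). The Procedure section places T0 before allocation. The item is absent from the list under Sociodemographic and clinical data, and no analysis in the Statistical analyses section names it.
- **Table 2 and Patient-reported health outcomes.** Choice is recorded at T2 and T3 only.
- **Randomization.** "Simple randomization stratified by site and patients’ surgical treatment options" is used, so preference is not a stratification factor.

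**The concern.** Choice has no T0 value of its own. The preference item is the closest baseline equivalent, is measured before allocation and is already in the questionnaire. As the rule is written, that item would probably stay out of the choice model: it is filed as a moderator, so it may not be screened at all. If it were screened, it would enter only after an observed difference between arms. A covariate earns its place by predicting the outcome; an imbalance screen selects on something else and makes the model depend on the data, here in an unblinded trial.

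What is at stake is the precision of one secondary comparison. It is still one that readers will look at, because the Intervention section describes the decision aid as balanced, and the choice result shows whether it shifts women toward or away from reconstruction.

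**Working it through.** **1. The plan's own figure.** The article powers only the d = 0.4 comparison. With two-sided alpha 0.05 and power 0.80:

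n per group = 2 × (1.960 + 0.842)² / 0.4² = 98.1, so 99 per group and 198 in total, as stated. With 20% attrition, 198 / 0.80 = 247.5, so 248 against the stated 250. These figures stand. None of them concerns choice.

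**2. What an imbalance screen lets through.** Assumptions: 99 women per arm, a 5% two-sided screen (the article sets no threshold), a preference–choice correlation of 0.5, and a choice SD of 0.46 (about √(0.7 × 0.3)).

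- Largest preference difference that passes: 1.96 × √(2/99) = 0.28 SD.
- Resulting shift in the unadjusted risk difference: 0.28 × 0.5 × 0.46 = 0.064, about 6 percentage points.
- For a typical imbalance of one standard error: √(2/99) = 0.14 SD, and 0.14 × 0.5 × 0.46 = 0.032, about 3 points.

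**3. Simulated effect of adding preference.** A logistic GEE was simulated with two visits per woman, an independence working correlation, robust standard errors, N = 200 (80% of 250), and 1,000 runs per scenario. The eight sites come from Study setting. All other inputs are assumptions:

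- choice treated as yes/no;
- preference split 10/10/20/25/35% from strongest against to strongest for;
- conditional treatment log odds ratio 0.8;
- sites of equal size, allocated exactly 1:1 within site, with site SD 0.3 or 0.8 on the logit scale;
- 8% of women without reconstruction at T2 having it by T3.

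Ratios and power compare the model with preference to the model without it. Ranges cover the two site SDs.

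| Log OR per preference point | Variance ratio, standardised risk difference | Power without | Power with |
|---|---|---|---|
| 0 | 1.00–1.01 | 0.68–0.75 | 0.68–0.75 |
| 0.5 | 0.92–0.93 | 0.60–0.66 | 0.64–0.70 |
| 1.0 | 0.76 | 0.47–0.48 | 0.60–0.61 |
| 1.5 | 0.59–0.61 | 0.31–0.32 | 0.48–0.49 |

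Power falls down the table because a fixed conditional odds ratio gives a smaller risk difference as preference explains more of the choice (0.16–0.18 in the first row, 0.10–0.11 in the last). The comparison to read is within rows. A ratio of 0.76 is worth 1/0.76 = 1.32 times the sample size for this outcome. With no treatment effect, a slope of 1.0 and site SD 0.5 (1,500 runs), rejection was 0.055 without preference and 0.050 with it.

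**4. The odds-ratio scale.** At slope 1.0 and site SD 0.3, the mean log odds ratio goes from 0.557 (SE 0.292) to 0.768 (SE 0.345). The SE rises, but the ratio rises too: 0.557/0.292 = 1.91 against 0.768/0.345 = 2.23. The adjusted odds ratio is a different, conditional quantity.

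**5. Site.** Adding site alone left the variance of the risk difference at 1.00 of unadjusted in every scenario and raised power by 0 to 4 points. This rests on exact balance within site, which the simulation imposed.

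**6. A second simulation.** This used one yes/no choice per woman, 99 per arm and 2,500 trials per scenario. With a preference–choice correlation of about 0.5, power rose from 83% to 91% (60% vs 78.7% choosing reconstruction) and from 81% to 90% (70% vs 86.5%). At correlations of 0.22–0.27, adjusted power was only about 82–84%, against about 81% unadjusted.

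**The case against.** The strongest reply is that silence is not exclusion. The article names a class of method for categorical outcomes and lists no covariates, and the covariate list of a secondary model is something an article commonly leaves to the full protocol or analysis plan. That stands: a reader might infer that site and preference are excluded from the GEE, and the text does not say so. What remains is the adjustment rule that the article does fix. It selects on observed difference, and the set it screens does not evidently contain preference.

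Four further points stand.

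- A reader might infer that leaving out site costs precision, since site is named for the decisional-conflict model. With site balanced by stratification, the simulation shows no variance gain.
- A claim that the unadjusted estimate is less precise fails for the log odds ratio. It holds for power and for the standardised risk difference, and the article names no effect measure for choice.
- The gain depends wholly on assumed choice rates and on an unknown link between preference and choice. All participants have been referred to a plastic surgeon, so preferences may be bunched and the link weaker.
- Choice is secondary, and nothing in the article feeds the GEE estimate into the cost model.

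The conditional rule could also admit preference if it were treated as a background characteristic and differed between arms. Section membership suggests that it would not be, and even then entry would be driven by the data.

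**Conclusion.** The point holds as an efficiency and robustness improvement to one secondary analysis. The stated rule probably leaves the natural baseline counterpart of choice out of its model, and it uses the wrong criterion for admitting covariates.

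Under the assumptions shown, prespecified adjustment lowers the variance of the standardised risk difference by 0% to about 40%. The power gain runs from nothing, through about 4–5 points for a weak link and 12–13 for a moderate one, to about 17 for a strong one. With no link the variance cost is at most 1%. The documents cannot say where in that range this trial lies.

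A reader might infer that the choice comparison is biased. It is not: randomisation protects it on average, and the exposure is to chance imbalance in a single trial. The primary analysis of decisional conflict and the sample size are untouched.

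**What to change.** In the Statistical analyses section, after the sentence on the GEE, state that:

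- the model for reconstruction choice includes the T0 preference score (1–5) as a covariate for women in both arms, whatever the observed balance;
- the stratification factors, site (small sites pooled) and surgical treatment options, are included for consistency with the randomisation, with no precision gain claimed for them;
- the arm effect is reported as a standardised risk difference with a confidence interval, with the unadjusted proportions by arm alongside.

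The cost is wording only, settled before the data are analysed: the item is already in the T0 questionnaire, and no new data, visits or participants are needed. The one small burden is the standardisation step, which is needed because the adjusted odds ratio is conditional on preference and is not comparable with an unadjusted one.
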